**Fig. 1 Fig1:**
[figure not shown]
Flow chart showing study protocol, recruitment, randomisation by stratification and final analysis

### Randomisation

Allocation of trial treatments will be provided through the local statistics department by a statistician who is not the trial statistician. Randomisation will be a 1:1 allocation using a computer generated randomisation schedule (using Stata Statistical Software: Release 14. College Station, TX: StataCorp LP) stratified by age and sex (four strata) using permuted blocks of size four. A seed was used as the random number generator to specify unique subject identifiers. The patient after being considered eligible for the study and consented by the orthopaedic trainee is stratified according to age and sex. The trainee then informs one of the coinvestigators who obtains the randomisation number from the previously generated schedule. The surgical team will be informed of the plate to be used, once randomised.

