### Consent procedures

Recruitment and consenting will be done by a trained research associate who will present the trial and interventions in a consistent and unbiased manner. Eligible patients will be provided with an information sheet and will have time to discuss their concerns prior to enrolment. (Patient Booklet and participation form-Additional file 1).

Inclusion Criterion and exclusion criterion are as shown in Table 1. Patients with isolated injuries in the upper limb were chosen so as to avoid the effect other injuries in the same limb could have and therefore bias the outcome. As most of the questionnaires are self-explanatory and to be filled in by patients themselves, reasonable proficiency in English is a pre-requisite.

**Table 1 Tab1:** POWIFF trial - Inclusion and exclusion criterion

Inclusion Criterion	Exclusion criterion
1. Age-18-80	1. Patients with concomitant injuries affecting treatment and rehabilitation of the affected arm
2. Pre-operative DASH score of 30 or less	2. Patients with associated neurovascular injuries requiring immediate surgery
3. Isolated closed distal radius fracture with shortening of radius of more than 3 mm, dorsal radial tilt of more than 10 degrees and an intra articular step of more than 2 mm.	3. Patients with associated significant carpal injuries, including scaphoid fractures
	4. Patient unlikely or unhappy to attend for follow up
	5. Patient with limited English proficiency
	6. Patient without cognitive capacity to consent and participate
	7. Patients with impaired upper limb function prior to injury enough to have a DASH score of more than 30 points

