### Recruitment

All patients eligible for the study, and for whom a decision to undergo surgical treatment by volar plating has been made will be invited to participate. Following patient recruitment to the trial, patients will be randomised to receive one or other of the plates. Patients declining randomisation will be managed using the routine plating option, but will still be monitored longitudinally in the standard fashion, forming an observational arm of the study. Inclusion of the patient in the trial will be flagged on their clinical notes by means of a trial sticker. (See Fig. 1). Documentation of complications such as implant failure, revision to another plate system and cross over will be done.

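### A single fixed block size of four at one centre with unblinded surgeons, and a co-investigator drawing numbers from a pre-generated schedule, leave allocation concealment inadequately protected

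*Protocol article*

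**What the plan says.** The Randomisation section sets the method in two statements: "Randomisation will be a 1:1 allocation using a computer generated randomisation schedule", and that this is "stratified by age and sex (four strata) using permuted blocks of size four". Generation is independent: "Allocation of trial treatments will be provided through the local statistics department by a statistician who is not the trial statistician". Consent comes before the number is drawn: "The patient after being considered eligible for the study and consented by the orthopaedic trainee is stratified according to age and sex". Then "The trainee then informs one of the coinvestigators who obtains the randomisation number from the previously generated schedule", and the surgical team is told which plate to use.

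Other sections give the context:

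- Study design: one centre.
- Blinding: patients, the collectors of the 12-month PRWE and the statistician are blinded; surgeons are not listed.
- Operative management: the operators are senior registrars, fellows and consultants.
- Trial organisation: every case is discussed at a daily departmental trauma meeting.
- Recruitment: trial patients carry a sticker on their notes, and "Patients declining randomisation will be managed using the routine plating option" while still being followed.

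On who recruits, Consent procedures differs from Randomisation: "Recruitment and consenting will be done by a trained research associate".

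**The concern.** Concealment requires that the person deciding whether to approach and enrol a patient cannot know or guess the next assignment. Three stated features work against this.

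- With one fixed block size, past allocations within a stratum reveal future ones.
- Surgeons at the single centre learn each plate, so past allocations can become known in the department that treats these patients.
- The independence of the list ends at generation, because a co-investigator and not the independent statistician goes to the schedule for each patient.

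The consent contradiction adds to this. It bears on whether the recruiter is a clinician of the department that learns the allocations.

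What is at stake is selection before randomisation. If the expected plate influences who is invited, or how firmly, the arms may differ at baseline. Blinded PRWE collection does not repair that, and adjustment reaches only the factors that were measured. There is room for selection: the Setting section gives about 200 operated fractures a year, so 2 × 200 = 400 over the 24-month recruitment period for 200 places, before eligibility is applied.

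**Working it through.** The protocol gives no figure for predictability, so there is none to reproduce. Its sample-size figures do reproduce. With a two-sided 5% level, 90% power, a difference of 11.5 and an SD of 20, a t-test needs 64.5, rounded up to 65 per group, and 65 × 1.5 = 97.5, rounded up to 98. The point does not depend on them; only the target of 200 (Trial organisation) is used below.

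**Inputs.** Block size 4, ratio 1:1 and four strata (Randomisation); 200 patients (Trial organisation). Assumption: patients fall into the four strata with equal probability, since stratum sizes are not given. It affects only the simulations.

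1. **Possible blocks.** 4!/(2!·2!) = 6 equally likely sequences: AABB, ABAB, ABBA, BAAB, BABA, BBAA.

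2. **Allocations known with certainty.** The 4th place is always forced. The 3rd is forced only in AABB and BBAA, that is 2/6 = 1/3. Expected forced places per block = 1/3 + 1 = 4/3, so the share is (4/3)/4 = 1/3. With complete blocks this is 200/3 = 66.7, about 67 patients.

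3. **Best guess by someone tracking each stratum.** The strategy is to guess the arm with more places left, and toss a coin if equal.
   - 1st place: 1/2.
   - 2nd place: 2/3.
   - 3rd place: forced with probability 1/3, otherwise a coin toss, so 1/3 + (2/3)(1/2) = 2/3.
   - 4th place: 1.
   - Sum = 17/6 = 2.833 of 4; share = 17/24 = 70.8%. In 200 patients that is about 142 correct guesses, against 100 by chance.

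4. **Less complete knowledge.** Simulating 200 patients in four equal strata gives 70.4% for an observer tracking balance within strata, and 60.6% for one tracking only the overall balance.

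5. **Effect of varying the block size.** For an observer who tracks stratum balance but not block boundaries, the guess rate is about 70% with fixed blocks of 4, 69% with blocks of 4 or 6, and 68% with blocks of 4, 6 or 8. Varying sizes mainly removes certainty about the last places; it hardly lowers the guess rate.

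6. **Who takes consent.** Consent procedures gives the task to a research associate and presents this as a means to an unbiased explanation. Randomisation says the patient is "consented by the orthopaedic trainee is stratified according to age and sex". As written, both cannot describe the same step.

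**The case against.** The strongest reply is that real safeguards are stated. A statistician outside the trial generates the list, eligibility and consent come first, the trainee does not hold the list, and the surgical team is told only afterwards. Storage and release of the list may be set out in the full protocol (V 1.2), which is not shown. All of this stands, and it rules out several stronger readings that a reader might infer:

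- **That concealment is defeated, or that the co-investigator sees what is coming.** The article does not say that later entries are visible, nor that this co-investigator recruits or operates. That full sight of a schedule would reveal every entry is true by definition and is no evidence that a recruiter has it.
- **That 71% and one third are the expected leak.** They need a known block size and a complete running tally in each of four strata over 24 months, with surgery spread over many operators.
- **That publication disclosed the block size throughout.** The article appeared on 30 April 2018 and recruitment was due to start in March 2017, so it could not have done so for roughly the first 13 of 24 months.
- **That the observational arm is a recruiter's exit.** The text describes it as the patient's choice, and following decliners helps to check for selective enrolment.
- **That no analysis could help.** Age and fracture severity can be at least partly adjusted for; unmeasured selection cannot.

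What the reply does not answer is the design as stated: one fixed block size, one centre, open surgeons, an investigator drawing the numbers, and two incompatible statements on consent.

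**Conclusion.** The point holds as a weakness that should be corrected, not as a demonstrated failure of concealment. The stated procedure leaves concealment inadequately protected. At most one third of allocations (about 67 of 200) could be known with certainty and at most 17/24 = 70.8% guessed, by someone in the department who knows the block size and tracks every allocation by stratum. If strata are ignored the figure is about 61%, assuming equal strata. The enumeration rests only on the stated block size and ratio. Whether anyone who recruits would have this knowledge is not something the article settles, and the consent contradiction leaves open who that person is. The sample size is unaffected.

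**What to change.** For the part of the schedule not yet used:

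1. **Main change.** Leave the list with the independent statistician who generated it, or in an equivalent locked system. Release one assignment at a time, only after the consented patient's trial number and stratum are irrevocably logged. If the full protocol already does this, the article should say so in place of the current co-investigator step.
2. **Secondary change.** Regenerate with randomly varying block sizes, for example 4 and 6, not disclosed to the site. The gain is mainly the loss of certainty about the last places in a block, so this does not replace step 1.
3. **Reconcile Consent procedures with Randomisation**, so that the research associate recruits and takes consent.

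The cost is a small administrative step at each randomisation and slightly looser balance. The largest possible difference between arms from unfinished blocks is half the block size per stratum: 4 × 2 = 8 patients over four strata with blocks of 4, and 4 × 3 = 12 if every open block were a 6.

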### Sample size

Sample size calculations were based on the requirement that effects be assessed at the 5% alpha level with 90% statistical power. It has been shown that the minimum clinically important difference on the PRWE is 11.5 points [28]. Assuming a standard deviation of 20 points, a sample of 65 patients per group would be required; following the application of a variance inflation factor of 1.5 to account for repeated measurements over time and patient attrition, a sample of 98 patients per group would be required.

### Blinding

The patients will be blinded as to which plate they have received until the conclusion of the study. The primary outcome (Patient-rated Wrist Evaluation (PRWE) scores at 12 months) will be collected by blinded researchers, and the statistician will be blinded to the treatment group.

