### Interventions

#### Operative management

The specific procedure for each patient managed operatively will be determined by the operating surgeon. Any adverse intra-operative and post-operative event will be recorded. All surgical procedures will be done by one of the senior orthopaedic registrars, trauma fellows or the orthopaedic consultants.

Operative time, plate size, data on the tourniquet time, radiation time and complications if any, and the number of times the metaphyseal screws have been exchanged will be recorded in both groups.

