#### Secondary outcomes

The DASH score is to be collected as a secondary outcome, in order to assess function of the whole upper limb, at 6 weeks, 3 months and one year [32]. The DASH score has a range from 0 to 100 with higher scores representing greater disability. Subjects rate task difficulty regardless of hand dominance or affected side, thus reflecting their total upper-extremity disability. Both the DASH and PRWE scores have been shown to be ideal and specific as a research tool for the upper limb [30]. The final DASH score at the end of 1 year will be used for definitive comparison between the 2 groups.The EQ5D (EuroQol) score will also be collected as a secondary outcome measure, at 3 months and one year. This score is a validated measure of health related quality of life, consisting of a 5 health domains as well as a separate VAS (Visual analogue) score. The five domains included in the EQ-5D are: mobility; self-care; usual activities; pain/discomfort and anxiety/depression. The EQ5D is the measure that tends to be most utilised in cost utility analysis [33] . The final EQ5D at the end of 1 year will be used for definitive analysis.Complications (including surgical site infection, unplanned surgery, implant failure, loss of reduction/screw breakout or implant fracture and post-operative nerve palsy up to one year) in both groups will also be documented and compared.Surgical data including operation time and screw numbersRadiographic indices including radial height, tilt and inclination and rates of non-union / delayed union and the Soong score will be analysed and compared in both groups.Soong score will be used to assess prominence and profile of the plate [17].The active range of motion (ROM)at the wrist and grip strength at 3 months and one year will be measured.Time to resumption of work and patient perceived percentage return of global function at 6 weeks, 3 months and 1 year.

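### Complications are compared between plates, but blinded collection is stated only for the 12-month PRWE, so unequal recording of judgement-dependent events is not excluded

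*Protocol article*

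**What the plan says.** **Status of complications.** The Aims section of the protocol article names safety alongside effectiveness and undertakes to document major and minor complications in both groups. Under Secondary outcomes the list is "Complications (including surgical site infection, unplanned surgery, implant failure, loss of reduction/screw breakout or implant fracture and post-operative nerve palsy up to one year", and these "in both groups will also be documented and compared".

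**Blinding.** The Blinding section has three elements:
- patients: "The patients will be blinded as to which plate they have received until the conclusion of the study"
- outcome collection: "The primary outcome (Patient-rated Wrist Evaluation (PRWE) scores at 12 months) will be collected by blinded researchers"
- analysis: "the statistician will be blinded to the treatment group"

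Blinded collection is stated for no other outcome.

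**Who knows the plate.** Under Randomisation, a co-investigator obtains the allocation from the schedule, and "The surgical team will be informed of the plate to be used, once randomised".

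**How events are recorded.** Operative management says: "Any adverse intra-operative and post-operative event will be recorded". The recorder is not named.

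**Contacts.** The Post-operative protocol section lists a clinical review with wound check and X-ray at 2 weeks, a telephone review with DASH and PRWE at 6 weeks, a clinical review with scores at 3 months, and a clinical review with X-ray and scores at 12 months. Secondary outcomes adds range of motion and grip strength at 3 months and one year, and also "Time to resumption of work and patient perceived percentage return of global function at 6 weeks, 3 months and 1 year".

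**The concern.** The PRWE is a self-completed questionnaire answered by patients who do not know their plate, so it is already well protected. The blinded collector is an extra safeguard. Several complications have no such protection. Whether redness is an infection, or tingling a nerve palsy, is partly a judgement, and nothing in the article keeps that judgement with someone unaware of the plate.

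This matters because the Aims section assumes that the new plate will do better, and the Background rests part of its rationale on less soft-tissue irritation and fewer flexor tendon problems. Staff who know the plate might watch a new device more closely and record more events, or be optimistic about it and record fewer. Neither randomisation nor a blinded statistician can undo a difference that arises when events are recorded. What is at stake is the between-plate complication comparison, not the primary PRWE analysis.

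**Working it through.** **Side-by-side reading**

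| Question | What the protocol article states | Section |
|---|---|---|
| Are complications compared between plates? | Yes, to one year | Secondary outcomes |
| Is the patient blinded? | Yes | Blinding |
| Is the statistician blinded? | Yes | Blinding |
| Is the outcome collector blinded? | Stated for the 12-month PRWE only | Blinding |
| Does the surgical team know the plate? | Yes | Randomisation |
| Who records complications? | Not stated | Recruitment; Operative management; Secondary outcomes |
| Who collects follow-up forms? | A research assistant, blinding status not stated | Data management |
| Is a complication enquiry listed at the contacts? | No; a wound check and X-ray at 2 weeks and an X-ray at 12 months are listed | Post-operative protocol |

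Recording by someone who knows the plate is therefore possible under the text. It is neither stated nor ruled out.

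**The plan's own figures.** The article gives no complication rate and no capture rate, so there is no figure on this point to reproduce. The only number taken from it below is n = 98 per group. That number reproduces: a difference of 11.5, SD 20, two-sided 5% and 90% power give 65 per group by the t calculation, and 65 × 1.5 = 97.5, rounded up to 98.

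**Illustration, all rates assumed.** Let the true risk p be the same in both arms, and let s₁ and s₂ be the fractions of events recorded.
- Recorded risks: p₁ = p·s₁ and p₂ = p·s₂.
- False difference: d = p(s₁ − s₂). Apparent risk ratio: s₂/s₁.
- Chance of a significant result in that direction: Φ[(d − 1.96·SE₀)/SE₁]. With p̄ the mean of p₁ and p₂, SE₀ = √[2p̄(1−p̄)/98] and SE₁ = √[p₁(1−p₁)/98 + p₂(1−p₂)/98]. With equal capture this chance is 2.5%.

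Worked case: p = 0.20, s₁ = 1, s₂ = 0.8.
- p₁ = 0.20, p₂ = 0.16, d = 0.04, p̄ = 0.18.
- SE₀ = √(2 × 0.18 × 0.82/98) = 0.0549.
- SE₁ = √[(0.16 + 0.1344)/98] = 0.0548.
- (0.04 − 1.96 × 0.0549)/0.0548 = −1.23, and Φ(−1.23) = 0.109.

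| True risk, both arms | Capture | Recorded risks | False difference | Apparent RR | Chance of significance in that direction |
|---|---|---|---|---|---|
| 5% | 100% v 80% | 5% v 4% | 1 point | 0.80 | 5.2% |
| 20% | 100% v 80% | 20% v 16% | 4 points | 0.80 | 10.9% |
| 20% | 90% v 70% | 18% v 14% | 4 points | 0.78 | 11.5% |
| 5% | 100% v 60% | 5% v 3% | 2 points | 0.60 | 10.6% |
| 20% | 100% v 60% | 20% v 12% | 8 points | 0.60 | 33.2% |

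A small imbalance does little: 80% v 75% capture of a 20% risk gives 16% v 15%, a ratio of 0.94. Either plate could be the one with lower capture.

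**The case against.** The best reply is that this is an article, not the full protocol. The Methods section refers to a protocol version 1.2, and Data management says that case report forms are designed separately. The name of the person who completes the complication form, and the items on it, may well be there. That stands, and the absence of those details is not itself the point. The scope of blinded collection, however, is not left elsewhere: the article states it and names one outcome at one time.

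Four stronger readings are tempting, and the documents do not support them.
- **That complication capture rests on surgeons who know the plate.** No section says so. The relevant sentences are passive, a research assistant coordinates visits and collects forms, and the oversight section adds review at the trauma meeting and by a committee that looks at safety.
- **That follow-up contacts collect only scores.** The 2-week review includes a wound check and X-ray. The 3-month review is clinical, with motion and grip measured. The 6-week time point also covers work and perceived function. None of these is a listed complication enquiry, but they are occasions on which events can be noticed.
- **That events between visits or treated elsewhere are lost and so bias the comparison.** The schedule shows no contact between 3 and 12 months, but the article does say that post-operative events are recorded. Because patients are blinded, any such losses should be roughly equal in the two arms. That would mainly cost completeness.
- **That the bias favours a particular plate.** Extra scrutiny and optimism act in opposite directions, so no direction is established.

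Two further points stand. Unplanned surgery and implant fracture leave little room for judgement. The assumed figures are also not alarming: 18% v 14% at 98 per arm gives z = 0.04/√(2 × 0.16 × 0.84/98) = 0.76, well short of 1.96.

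**Conclusion.** The point holds in a limited form. Complications are compared between plates and serve the safety aim, blinded collection is stated only for the 12-month PRWE, the surgical team knows the plate, and no uniform complication enquiry is listed at the scheduled contacts. Unequal recording of judgement-dependent events, chiefly infection and nerve symptoms, is therefore not excluded, and it could run either way.

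The size cannot be derived from the documents. Under assumed equal true risks of 5% to 20% and 98 per arm, capture of 80% in one arm against full capture in the other gives a false difference of 1 to 4 points. The chance of a significant result in that direction is then about 5% to 11%, instead of 2.5%. At 60% capture the figures are 2 to 8 points and about 11% to 33%. With nearly equal capture the effect is negligible.

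This is a worthwhile, low-cost improvement to a secondary comparison. It does not show that complications will be recorded with bias, and it does not touch the primary outcome.

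**What to change.** Extend the Blinding section so that researchers blinded to the plate put one fixed complication checklist to every randomised patient at the existing 6-week, 3-month and 12-month contacts. It should ask, since the last contact, about infection, nerve symptoms, further wrist surgery or plate removal, and treatment elsewhere. Use the answers for patient-reportable events in the between-plate comparison.

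The checklist cannot be the only source. Implant failure, loss of reduction, screw breakout and intra-operative events need operative, hospital and X-ray records. Combine these with the checklist and apply the same written definitions in both arms. State who records and classifies these events and whether that person knows the plate.

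Cost: a few more minutes per contact, and some reconciling of patient reports with hospital records. The 6-week and 3-month collectors must also be kept blinded, which the article does not currently state. X-ray-based events cannot be fully masked because the plate is visible, so for them common definitions are the main protection.
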